## Abstract

Background

Caregivers of children with congenital heart disease (CHD) often experience stress, uncertainty, and challenges in managing their child’s care after hospital discharge. A structured transition care approach can help ease this process by improving caregivers' preparedness, awareness, and satisfaction with post-discharge care.

Objective

This study aims to develop and evaluate a nurse-led transition care guidance (TCG) program to enhance caregivers' readiness, awareness, and satisfaction during the transition from hospital to home care for children with CHD.

Method

A mixed-methods approach was used, consisting of a quasi-experimental quantitative phase to assess the effectiveness of the TCG intervention by comparing caregivers' readiness and satisfaction scores before and after implementation and qualitative focus group discussions (FGDs) to explore caregivers' unmet needs and challenges during the transition process.

Data sources include caregiver surveys, post-discharge follow-up interviews, and hospital records. Thematic analysis will be conducted on FGDs to identify key issues affecting caregivers.

Results

The intervention is expected to improve caregivers' ability to provide care, increase their understanding of medical needs, and enhance their overall satisfaction with the transition process. Qualitative findings will highlight common challenges and gaps in post-discharge support.

Conclusion

This study will contribute to the development of evidence-based transition care plans that optimize the hospital-to-home transition for children with CHD. It highlights the importance of structured, nurse-led interventions to improve post-discharge outcomes for both caregivers and patients.

## Introduction

Congenital heart disease (CHD) remains a significant contributor to childhood morbidity, necessitating meticulous care and prolonged management. The transition from hospital to home poses multiple challenges for caregivers, who must navigate intricate medication schedules, vigilantly monitor health statuses, and promptly identify early signs of complications. A prevalent issue among caregivers is the sense of inadequacy and heightened anxiety, often stemming from insufficient education on effective management strategies [1,2].​

Existing literature reveals a scarcity of structured, evidence-based interventions specifically designed to support caregivers of children with CHD during the post-discharge transition. Notably, nurse-led interventions have demonstrated efficacy in enhancing outcomes across various patient populations; however, their application within pediatric CHD care remains underexplored. For instance, a study conducted in Southern India evaluated a structured nurse-led parent discharge teaching program and found that both nurses and parents exhibited significant improvements in home care knowledge post-implementation. Additionally, there was a notable reduction in surgical site infections among children, underscoring the program's effectiveness in promoting better home care practices after cardiac surgery [3,4].

Similarly, a quasi-experimental study in Thailand assessed the impact of a discharge planning program on caregivers' behaviors for children with CHD post-heart surgery. The findings indicated that caregivers who participated in the program demonstrated significantly improved caring behaviors compared to those who received routine care, highlighting the program's potential to enhance caregiver preparedness and reduce post-discharge complications [5-7].

To address these challenges and bridge the existing gap, this study aims to develop and evaluate a comprehensive nurse-led transition care guidance (TCG) program. The primary objectives are to enhance caregiver knowledge, bolster readiness for discharge, and elevate satisfaction with the transition process. By implementing a structured TCG program, we aspire to empower caregivers with the necessary tools and confidence to manage their children's care effectively post-discharge, thereby improving overall health outcomes for children with CHD.

This study is among the first to develop and evaluate a nurse-led TCG program specifically tailored for caregivers of children with CHD. Unlike previous interventions, which focus on one-time discharge education, this study aims to establish a structured, ongoing support system that extends into the post-discharge period. By incorporating follow-up strategies, personalized guidance, and caregiver engagement, this program seeks to bridge the gap between hospital discharge and sustained home care readiness. Furthermore, this study will contribute to a framework for nurse-led pediatric transition care, which is currently underdeveloped in CHD management.

To address these challenges and bridge the existing gap, this study aims to develop and evaluate a comprehensive TCG program. The primary objectives are to enhance caregiver knowledge, bolster readiness for discharge, and elevate satisfaction with the transition process. By implementing a structured TCG program, we aspire to empower caregivers with the necessary tools and confidence to manage their children's care effectively post-discharge, paving the way for an evidence-based, scalable model for pediatric CHD transition care.

Objectives

The primary objectives of this study are to identify the challenges and unmet needs faced by caregivers during the transition of children with CHD from hospital to home; develop a nurse-led TCG program tailored to address these identified needs; evaluate the effectiveness of the TCG intervention in improving caregiver knowledge, readiness for discharge, and satisfaction.

The secondary objectives are to assess caregiver confidence in managing care tasks, the number of post-discharge complications, and the impact of the intervention on hospital readmission rates.

## Materials and methods

This study will have a mixed-methods design, incorporating both qualitative and quantitative approaches to address the research questions. The qualitative phase will involve focus group discussions (FGDs) with caregivers, nurses, and physicians to understand the challenges and unmet needs faced by caregivers during the transition of children with CHD from hospital to home. Multi-stakeholder opinion on transition care will help identify the gaps in caregiver preparedness and inform the development of the nurse-led TCG program. The qualitative data will be analyzed using thematic analysis, which will allow the identification of common themes and patterns in the experiences and challenges reported by the participants.

In the quantitative phase, a quasi-experimental design with a pre-test and post-test control group will be used to evaluate the effectiveness of the nurse-led TCG program. The intervention group will receive the TCG program, which will include pre-discharge education sessions, personalized discharge care guides, and telephonic follow-up support at specified intervals post-discharge. The control group will receive standard discharge instructions without the additional components of the TCG program.

The study will take place in the pediatric care units of a tertiary care hospital. The participants will include caregivers of children diagnosed with congenital heart disease who are preparing for discharge. Inclusion criteria will include caregivers who are the primary decision-makers and care providers for the child and caregivers of children with congenital heart disease who are scheduled for discharge from the pediatric care unit. Exclusion criteria will include caregivers who have limited language proficiency, caregivers who are unable to attend the intervention sessions, and caregivers who are unable to commit to the follow-up process due to logistical or other reasons.

The control group will receive the standard discharge care provided by the hospital, which includes routine discharge instructions given by healthcare providers before the child is discharged. This typically consists of verbal guidance on medication administration, follow-up appointments, basic home-care instructions, and emergency signs to watch for. However, caregivers in the control group will not receive the additional structured components of the nurse-led TCG program. Specifically, they will not have access to personalized discharge care guides, structured pre-discharge education sessions, or scheduled telephonic follow-up support.

The control group caregivers will still undergo a pre-discharge assessment to evaluate their initial knowledge and readiness for discharge. During the follow-up period, their experiences and post-discharge outcomes will be assessed at 7, 15, 30, and 45 days after discharge through surveys and telephone interviews. Data from the control group will serve as a baseline for comparison with the intervention group to determine the effectiveness of the TCG program in improving caregiver preparedness, confidence, and child health outcomes.

The nurse-led TCG program will be developed based on the findings from the qualitative phase and will focus on key areas, such as medication administration, signs of deterioration, feeding techniques, emergency management, and other essential aspects of post-discharge care. The program will also include the provision of a personalized discharge care guide, which will contain instructions on daily care, emergency contact numbers, follow-up schedules, and signs to watch for in the child’s health. Additionally, caregivers in the intervention group will receive telephonic follow-up at 7, 15, 30, and 45 days post-discharge to ensure they have the opportunity to ask questions, reinforce learning, and receive additional support as needed.

The primary outcome measures for this study will include caregiver knowledge of CHD and its management, caregiver readiness for discharge, and caregiver satisfaction with the transition process. Caregiver knowledge will be assessed using a congenital heart disease knowledge scale (CHDKS), which will be developed specifically for this study and validated for reliability and accuracy before data collection. Similarly, caregiver readiness for discharge will be evaluated using a readiness for discharge scale, which will be developed and subjected to rigorous validity and reliability testing. Caregiver satisfaction will be measured through a satisfaction survey assessing their experience with the discharge process, the information provided, and the support received; this tool will also undergo validity and reliability testing before implementation. All research instruments will be carefully developed and tested for content validity, construct validity, and reliability to ensure accurate and meaningful measurement of study outcomes.

Secondary outcomes will include caregiver confidence in managing care tasks, including medication administration and recognizing emergency signs in the child, as well as hospital readmission rates and post-discharge complications within 30 days of discharge. A caregiver confidence assessment tool will be developed specifically for this study and validated for reliability and accuracy before data collection. Hospital readmission rates and post-discharge complications will be tracked using hospital records and follow-up interviews. These outcomes will help assess the broader impact of the nurse-led TCG program on both caregiver preparedness and child health outcomes.

Data collection will be conducted at three time points: baseline (at the time of admission), during discharge, and post-discharge follow-up (starting from seven days after discharge). At baseline (admission), caregiver surveys will be conducted to assess their initial knowledge, readiness, and confidence in managing care. During discharge, post-assessment will be carried out to evaluate changes in caregiver preparedness and understanding after receiving the nurse-led TCG. Post-discharge follow-up, starting from seven days after discharge, will involve caregiver surveys, telephone interviews, and a review of medical records to track hospital readmission rates and post-discharge complications up to 45 days after discharge. The qualitative data will be collected through FGDs, which will be audio-recorded, transcribed, and analyzed using thematic analysis. Quantitative data will be analyzed using statistical methods such as paired t-tests for comparing pre- and post-intervention measures, independent t-tests to compare the intervention and control groups, and multiple regression analysis to identify predictors of caregiver satisfaction and readiness for discharge.

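### The pre-test time point is stated inconsistently; if it falls later in controls than in the programme group, change scores would favour the programme

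*Protocol article*

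**What the plan says.** All the relevant statements are in the Materials and methods section of the protocol article.

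- **Design.** The quantitative phase is described as "a quasi-experimental design with a pre-test and post-test control group will be used to evaluate the effectiveness".
- **Who enters.** "The participants will include caregivers of children diagnosed with congenital heart disease who are preparing for discharge". The inclusion criteria repeat this: "caregivers of children with congenital heart disease who are scheduled for discharge from the pediatric care unit". Both statements cover both groups.
- **General schedule.** "Data collection will be conducted at three time points: baseline (at the time of admission), during discharge, and post-discharge follow-up". The first of these is specified further: "At baseline (admission), caregiver surveys will be conducted to assess their initial knowledge, readiness, and confidence in managing care". No group is named.
- **Controls.** "The control group caregivers will still undergo a pre-discharge assessment to evaluate their initial knowledge and readiness for discharge". The only later control assessments that the same paragraph lists are at 7, 15, 30 and 45 days after discharge.
- **Discharge post-test.** "During discharge, post-assessment will be carried out to evaluate changes in caregiver preparedness and understanding after receiving the nurse-led TCG". Controls do not receive the TCG.
- **Tests.** The plan lists "paired t-tests for comparing pre- and post-intervention measures, independent t-tests to compare the intervention and control groups". It does not say whether the between-group test uses post-scores or changes.

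**The concern.** Three descriptions of the starting point do not fit together. The initial measure is at admission in the general schedule and at a pre-discharge assessment in the control-group text. The eligible population is defined by a status, scheduled for discharge, that a child does not normally have on admission. A site that recruits by that criterion would usually meet the caregiver after the admission survey was due.

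The study is described as quasi-experimental and no randomisation is mentioned. A pre-test taken at the same moment in both groups is therefore the main means of seeing, or allowing for, differences that existed before the programme. Knowledge and readiness are primary outcomes and confidence is secondary; these are the three measures surveyed at baseline.

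Suppose a site applied the admission baseline to the TCG group and the pre-discharge assessment to controls. Whatever caregivers learn during the stay, and possibly from routine instruction, would then lie inside the TCG group's change but be absorbed into the controls' baseline. A programme with no effect would appear to have one.

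**Working it through.** **Setting the statements side by side**

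| Item | General schedule | Control-group text | Eligibility |
|---|---|---|---|
| Initial measure | At admission, no group named | Pre-discharge assessment | Child already scheduled for discharge |
| Content | Knowledge, readiness, confidence | Knowledge, readiness | – |
| Post-test at discharge | Worded as following the TCG | Not mentioned | – |

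The statements can be reconciled in more than one way:

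1. Both groups have the admission survey, and pre-discharge is a loose label for it. Timing is then equal, but eligibility still conflicts with admission.
2. Both groups have their pre-test once discharge is planned. Timing is then equal, but the words placing the baseline at admission are wrong.
3. The TCG group is measured at admission and controls near discharge. Timing then differs by group.

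Only the third produces a bias between groups.

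**Size of the bias under the third reading**

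Let m be the mean score at admission, d the usual-care gain from admission to the controls' pre-test, and e the further usual-care gain up to the post-test. With no programme effect:

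- TCG change = (m + d + e) − m = d + e
- Control change = (m + d + e) − (m + d) = e
- Difference in change = d

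The bias is the whole of d, whatever the sample size.

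**Illustrative false-positive rate**

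The article gives no sample size, significance level, standard deviation or effect size, so there is no planned figure to reproduce. The following inputs are assumptions: two-sided 5% level, score SD of 1, pre-post correlation r = 0.5, no true effect, and a normal-approximation test of the between-group difference in change.

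- SD of change = √(2(1 − r)) = √(2 × 0.5) = 1
- Standard error of the difference = √(2/n); for n = 50 per group, √0.04 = 0.2
- Rejection rate = [1 − Φ(1.96 − d/SE)] + Φ(−1.96 − d/SE)

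For n = 50 and d = 0.3, d/SE = 1.5. The rate is [1 − Φ(0.46)] + Φ(−3.46) = 0.323.

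| Offset d (SD) | 30 per group | 50 per group | 100 per group |
|---|---|---|---|
| 0 (equal timing) | 5.0% | 5.0% | 5.0% |
| 0.1 | 6.7% | 7.9% | 10.9% |
| 0.2 | 12.1% | 17.0% | 29.3% |
| 0.3 | 21.3% | 32.3% | 56.4% |
| 0.5 | 49.1% | 70.5% | 94.2% |

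A higher pre-post correlation raises these rates. At r = 0.7 the SD of change is √0.6 = 0.775, and with 50 per group an offset of 0.2 SD gives about 25% instead of 17%.

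**The case against.** The strongest reply is that nothing in the article says the groups are measured at different times. The general schedule is a single schedule with no group named. The word *still* in the control-group text suggests that controls have the same assessment although they do not receive the TCG. Pre-discharge literally covers any moment before discharge, admission included. The declared design has a pre-test and a post-test with a control group, so the TCG-specific wording of the post-test may be only loose phrasing. Eligibility applies to both groups alike: it makes an admission baseline hard to collect but creates no difference between groups. An article may also leave a group-by-group assessment table to the full protocol.

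Most of this stands. A reader might infer that pre-post change is already not comparable between the groups, that controls have only one measurement around discharge, or that the admission pre-test cannot exist. The documents support none of these. Each takes the least favourable of several permitted readings, and the eligibility text fixes no enrolment day.

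A reader might also take the rejection rates as a property of the planned analysis. They are not. The plan does not specify a between-group test of change, and the Results section expects higher knowledge scores than in controls, which reads as a comparison of post-scores. Baseline timing does not bias that comparison.

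The reply does not remove the inconsistency. This is not detail left out: the admission baseline and the eligibility rule are both stated and do not fit on any of the readings. With no randomisation described, a post-score comparison without a comparable baseline cannot show whether the groups differed at the start.

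**Conclusion.** The concern holds as an inconsistency with a conditional consequence. The pre-test moment is given in ways that cannot all be followed, and it is not stated that controls complete the discharge post-test.

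If the pre-test falls later in controls than in the TCG group, change scores and baseline comparability for knowledge, readiness and confidence would be distorted in the programme's favour, by the full usual-care gain between the two moments. If the timing is the same in both groups, this bias is zero.

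The illustrated range, from the nominal 5% to about 70% with 50 per group, depends on the assumed offset, group size and correlation and on testing the difference in change. None of these is in the article. The direction of the bias requires only that caregivers' scores rise under usual care during the stay.

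Satisfaction is not in the baseline survey, and readmissions and complications have no pre-test. These outcomes are outside the problem.

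**What to change.** Reconcile the eligibility, control-group and data-collection text to one schedule that applies to both groups:

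1. **Pre-test.** The same instruments at one defined moment, before any TCG session and before routine discharge instruction. List the same measures for both groups; confidence is missing from the control-group sentence.
2. **Eligibility.** Make it compatible with that moment. Either enrol at admission and reword the criterion, or enrol when discharge is planned and drop the statement that the baseline is at admission.
3. **Post-test.** The same assessment at discharge, completed by controls after standard instructions and by the TCG group after the programme. Say explicitly that controls complete both assessments.

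The cost is a few sentences of protocol text and, at most, one survey administration in controls that the declared design already implies. This should be settled before enrolment, because a pre-test that is missed or taken at the wrong moment cannot be recovered.

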## Results

The primary aim of the study is to assess the effectiveness of the nurse-led TCG program in improving caregiver knowledge, readiness for discharge, and satisfaction with the care transition process. We anticipate that caregivers in the intervention group will show improved knowledge of CHD management, as indicated by higher scores on the CHDKS compared to caregivers in the control group. This improvement is expected to reflect the enhanced education provided through the TCG program, which includes pre-discharge education sessions and a personalized care guide.

Caregiver readiness for discharge is also expected to improve significantly in the intervention group. The readiness for discharge scale will measure how well caregivers feel prepared to manage the child’s care once at home. We hypothesize that caregivers in the intervention group will report higher levels of preparedness due to the additional support provided through the TCG program, which will include structured follow-up and the ability to address any questions or concerns during the post-discharge period.

Additionally, we expect caregiver satisfaction to be significantly higher in the intervention group compared to the control group. The caregiver satisfaction survey will measure satisfaction with the discharge process, the clarity of the information provided, and the level of support received. It is anticipated that caregivers who receive the nurse-led TCG will report greater satisfaction, as the program is designed to address their specific needs and provide continuous support after discharge.

Secondary outcomes will include increased caregiver confidence in managing key aspects of care, such as medication administration and recognizing emergency signs in their child. We expect that caregivers in the intervention group will report greater confidence in these areas, which could translate to a lower likelihood of post-discharge complications and fewer hospital readmissions. Hospital readmission rates and the number of complications within 30 days post-discharge will be tracked as secondary indicators of the effectiveness of the transition care intervention.

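### The only assessment labelled 'post' is taken at discharge, before any telephone support, and no primary comparison is tied to a time point or adjusted for baseline

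*Protocol article*

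**What the plan says.** In the protocol article, Materials and methods, the design is "a quasi-experimental design with a pre-test and post-test control group will be used to evaluate the effectiveness of the nurse-led TCG program". No randomisation is described.

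The programme has three parts: "pre-discharge education sessions, personalized discharge care guides, and telephonic follow-up support at specified intervals post-discharge". The calls are dated in the same section: "caregivers in the intervention group will receive telephonic follow-up at 7, 15, 30, and 45 days post-discharge". For the control group, "their experiences and post-discharge outcomes will be assessed at 7, 15, 30, and 45 days after discharge through surveys and telephone interviews".

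The data-collection paragraph gives the schedule: "Data collection will be conducted at three time points: baseline (at the time of admission), during discharge, and post-discharge follow-up". Admission is the baseline for knowledge, readiness and confidence. The discharge survey is the post-assessment, and its purpose is "to evaluate changes in caregiver preparedness and understanding after receiving the nurse-led TCG". Follow-up starts at day 7, runs to day 45 and includes caregiver surveys, but the article does not name the scales used in them.

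The methods, introduced as examples, are paired t-tests for pre against post, independent t-tests between groups, and multiple regression for predictors of satisfaction and readiness. None is assigned to a visit.

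The Results section expects caregivers in the intervention group to report "higher levels of preparedness due to the additional support provided through the TCG program, which will include structured follow-up", and it links higher satisfaction to continuing support after discharge.

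**The concern.** The description of the discharge assessment does not fit the programme as the article defines it. At discharge a caregiver in the intervention group has had the education sessions and the guide, but no call. If the pre-post change, or the group difference, is read at discharge in the article's own terms, the primary result concerns the pre-discharge components and would be reported as the effect of the whole programme.

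This touches the study's main claim. The Introduction distinguishes the programme from one-time discharge teaching by the support that continues afterwards. A result at discharge cannot support that distinction, and it cannot test the part of the readiness and satisfaction hypotheses that rests on later support.

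Two further gaps follow. The article does not say which assessment carries each primary comparison, and satisfaction has no assigned time at all. The between-group test it names also makes no allowance for groups that differ at the start, which is a real risk without randomisation.

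**Working it through.** The article states no sample size, alpha, effect size or SD, so there is no figure of its own to reproduce.

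**Step 1. Calls delivered by each assessment.** Inputs: call days 7, 15, 30 and 45, and assessments at discharge and on the same four days (Materials and methods; the assessment days are stated for the control group).

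| Assessment | Calls on earlier days | Calls including that day |
|---|---|---|
| Discharge | 0 of 4 | 0 of 4 |
| Day 7 | 0 of 4 | 1 of 4 |
| Day 15 | 1 of 4 | 2 of 4 |
| Day 30 | 2 of 4 | 3 of 4 |
| Day 45 | 3 of 4 | 4 of 4 |

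A discharge comparison contains none of the delivered telephone component. A day-45 comparison contains three or four of the four calls.

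**Step 2. Rationale against timing.** Knowledge is expected to rise because of the education sessions and guide, so a discharge measurement fits. Readiness is credited partly to structured follow-up and to answering questions after discharge. No question can have been answered in a call by the time of discharge. Satisfaction is credited partly to continuing support, and no time is given for its survey.

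**Step 3. Unadjusted two-sample comparison without randomisation.** Assumed inputs, none from the article: true effect δ = 0.50 SD, baseline-outcome correlation ρ = 0.5, baseline imbalance Δ favouring the intervention group. The expected unadjusted difference is δ + ρΔ.

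- Δ = 0: 0.50 + 0.5 × 0 = 0.50 SD
- Δ = 0.2: 0.50 + 0.5 × 0.2 = 0.60 SD
- Δ = 0.4: 0.50 + 0.5 × 0.4 = 0.70 SD

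A simulation with 50 caregivers per group gave 0.50, 0.60 and 0.70. An imbalance in the other direction would lower the estimate by the same amount.

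**Step 4. Illustration of leaving the time point open.** Assume one scale is tested at five post-baseline visits (discharge and days 7, 15, 30 and 45), each at 5%, with any significant result counted as success. For independent tests the chance of at least one false positive is 1 − 0.95^5 = 0.226. For equally correlated test statistics it is P(max |Z| > 1.96):

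- correlation 0.5: 18.3%
- correlation 0.7: 14.8%
- correlation 0.8: 12.7%

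If only the four follow-up visits are counted, correlations of 0.5 to 0.8 give 15.6% to 11.4%, and independence gives 1 − 0.95^4 = 18.5%.

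**The case against.** The strongest reply is that the article is a condensed account. The ranking of time points, the repeated-measures model and the handling of missing scores commonly sit in an analysis plan that is not shown here. That is fair, and the lack of a mixed model is not in itself the point. What the reply does not reach is the text that is printed: the discharge survey is said to follow receipt of a programme that is not yet complete, and the named between-group test is unadjusted in a non-randomised design.

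Several stronger readings are tempting, and the article does not support them.

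- A reader might infer that the plan cannot measure the effect of the full programme. It can if the scales are repeated at follow-up: an independent comparison at day 45 would come after three or four calls.
- A reader might infer that the later assessments are to receive only two-sample t-tests. The article assigns no test to any visit, offers its methods as examples and also lists regression. A paired test against a later survey is not excluded, and a paired test does use the correlation within a caregiver.
- A reader might count six assessments against the stated three. The third item is a follow-up period running to day 45, and the four dated contacts fall inside it. It reads as a label for phases and is not a real contradiction.
- A reader might take 13% to 18% as this trial's error rate. It requires every scale to be repeated at five visits, which the article nowhere states.

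It can also be argued that readiness concerns how prepared caregivers feel for care at home, so knowing that calls are scheduled might raise the discharge score. That is plausible, but it would be an effect of expecting support and not of receiving it.

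**Conclusion.** The point holds as a mismatch of timing and interpretation, together with a weak named comparison. By the article's own dates, the assessment labelled as post follows 0 of 4 calls. A result at discharge speaks to the sessions and the guide, while the stated hypotheses for readiness and satisfaction reach further. This part rests on no assumption.

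The size of the statistical consequence does rest on assumptions. At a baseline-outcome correlation of 0.5, imbalances of 0.2 to 0.4 SD would move an unadjusted estimate by 0.1 to 0.2 SD. The false-positive range of about 13% to 18%, for correlations 0.8 to 0.5, only illustrates what an open choice among five visits could cost. The matter should be corrected, but the data needed may already be planned, so it does not undermine the study.

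**What to change.** - Describe the discharge assessment as measuring the pre-discharge components only, and bring the readiness rationale in the Results section into line with that.
- Name one primary time point for each primary outcome. For any outcome meant to reflect the whole programme, use a follow-up survey after calls have been made, for example day 45, and confirm that its scale is repeated then in both groups.
- Replace the t-tests as the primary comparison with a baseline-adjusted model: ANCOVA at the primary time point, or a mixed model over the repeated assessments if the scales are repeated. Treat other time points as secondary.
- Satisfaction has no baseline score, so adjust it for caregiver and child characteristics.

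The cost is revised wording and slightly more modelling. Knowledge and readiness already have an admission score. The sponsor must confirm which scales are repeated at follow-up; if a scale needed at the primary time point is not, it would have to be added to a survey contact that is already planned. Adjustment removes only the imbalance that is measured, so some confounding may remain in a non-randomised comparison.
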